### Selection of Subjects

Subjects of both genders will be recruited in two centers: the Multiple Sclerosis Center of the Sapienza University of Rome and the Multiple Sclerosis Center of the IRCCS Regina Elena National Cancer Institute. The planned recruitment period will be of three years.

Prior to enrollment, all participants will be screened to check their inclusion and exclusion criteria.

Patient inclusion criteria will be:

Patients diagnosed with relapsing-remitting MS (93)Patients untreated or treated with only immunomodulatory therapy18–60 years old

Patient exclusion criteria will be:

pregnancyco-existing neoplastic, hematologic, thyroid, metabolic, thrombotic, or autoimmune diseasesdrug or alcohol addictedtherapy with immunosuppressive drugs, steroids, or any medication interfering with coagulation

We will evaluate 3 groups of subjects: 30 RRMS patients in relapse (Group I); 30 RRMS patients in remission, i.e., without relapse in the previous 2 months (Group II), and 30 sex- and age-matched healthy controls (Group III).

A relapse or exacerbation or “attack” was defined by the multiple sclerosis guidelines as a manifestation of new or worsened neurological symptoms lasting for more than 24 hours (94). Symptoms should be supported by subjective description and by objective clinical assessment with no other explanation for them. The relapse is separated from the previous “attack” by at least 30 days and usually persists for days or weeks, then slowly improves over weeks or a few months ending with partial or complete recovery, i.e., remission. MRI showed the new and/or active lesions in the majority of patients, and steroid therapy often accelerates the recovery of symptoms.

Relapse needs to be distinguished from a pseudo-exacerbation, which is defined as a temporary worsening of pre-existing symptoms without new MS-related neuroinflammation, thus an MRI does not detect active or new lesions (95). The causes of pseudo-relapses could be different and include infections with or without fever, increased body temperature due to over-exercising, sauna, hot shower/bath or weather, dehydration, hormonal changes during menstruation or severe psychological stress, surgery, trauma, medications, alcohol overuse, and several medical conditions as thyroid or other metabolic disorders. Pseudo-relapses usually last less than 24 hours and resolve after removing their triggering causes with no need for steroid therapy.

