### Data Analysis

#### Sample Size Calculation

Overall 90 subjects (30 for each group) will be enrolled to compare the level of complement C4a (55). By using the ANOVA test, this sample size will allow detection of effect size values [delta=(miA–miB)/sigma] equal to at least 0.71, with a statistical power of 80%, to a level of significance of 5%.

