#### Statistical Methods

Descriptive statistics will be used to summarize pertinent study information. Correlations between quantitative variables will be assessed with the Pearson r correlation. The associations will be analyzed by the Fisher exact test or Chi Square test for trends. Comparisons between disease subgroups and control group will be carried out for different variables, using either Student’s *t-*test or analysis of variance (ANOVA). If the ANOVA shows a statistical difference between subgroups, a post-hoc analysis with Bonferroni correction for multiple comparisons will be performed. For non-normally distributed data, non-parametric (Mann Whitney-U or Kruskal-Wallis-H) tests will be used. The level of significance is set at p ≤ 0.05 (SPSS version 20.0, SPSS Inc., Chicago, Illinois, USA).

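### With exactly three groups, a Bonferroni step after a significant ANOVA is not needed to hold the within-marker error at 5%, and it costs power on the relapse contrasts

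*Protocol article*

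**What the plan says.** All references are to the protocol article.

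- **Groups.** Selection of Subjects fixes three groups of 30: patients in relapse, patients in remission, and matched healthy controls. That makes three pairs, two of which involve relapse.
- **Decision rule.** Statistical Methods compares the groups by t-test or ANOVA and adds: "If the ANOVA shows a statistical difference between subgroups, a post-hoc analysis with Bonferroni correction for multiple comparisons will be performed". It also states: "The level of significance is set at p ≤ 0.05".
- **Power.** Sample Size Calculation bases the 90 subjects on the ANOVA, at 80% power and a 5% level, and gives the detectable difference as "effect size values [delta=(miA–miB)/sigma] equal to at least 0.71". No power is given for the pairwise comparisons.
- **Rank route.** "For non-normally distributed data, non-parametric (Mann Whitney-U or Kruskal-Wallis-H) tests will be used". No post-hoc rule is given after a Kruskal-Wallis test.

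The article gives no reason for using both the ANOVA gate and the Bonferroni correction.

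**The concern.** The abstract asks whether markers differ between patients in relapse and both patients in remission and healthy controls. Those are pairwise questions. Under the stated rule, a pair counts as different only if the three-group test passes at 5% and the pair then passes at 5%/3 = 1.67%. Both layers guard against the same thing, namely a false claim among the three comparisons of one marker. With three groups the first layer is enough. The second therefore uses up power on the comparisons of most interest, with the sample fixed at 30 per group and the stated 80% covering only the omnibus test.

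**Working it through.** **Inputs.** From the article: three groups, n = 30 each, effect 0.71 SD, alpha 0.05. Assumed, because not stated: two-sided tests, Bonferroni over all three pairs, and (until step 5) normal data with equal variances.

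**1. Reproduce the plan's figure.** One-way ANOVA has df (2, 87) and noncentrality λ = n·Σ(μᵢ − μ̄)².
- Relapse 0.71 SD from two equal groups: λ = 30 × 0.71² × 2/3 = 10.08, power 80.4%. This matches the stated 80%.
- Evenly spaced means (0.71, 0.355, 0): λ = 30 × 0.71²/2 = 7.56, power 67.5%.

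The first layout is therefore the one behind the sample size, and it serves as the design point below.

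**2. Why the gate suffices.** Call the groups A, B and C. If any two of A = B, A = C, B = C are true, all three are true. The only intersection hypothesis is therefore that all three means are equal, which the ANOVA tests at 5%.
- All means equal: a false claim needs a significant ANOVA, so the error is at most 5%.
- Means not all equal: at most one pair is truly equal, and it is tested at 5%, so the error is again at most 5%.

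This is strong family-wise control within a marker. The argument does not extend to four or more groups.

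**3. What Bonferroni costs one contrast.** The standard error of a difference is √(2/30) = 0.258 SD, so a true difference of 0.71 SD gives an expected t of 0.71/0.258 = 2.75. The critical value on 87 df is 1.99 at 5% and 2.44 at 1.67%. By the normal approximation, power at the stricter level is Φ(2.75 − 2.44) ≈ 62%. At the 5% level it is Φ(2.75 − 1.99) ≈ 78% before the gate, and simulation gives 73% with the gate.

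**4. Simulation** (200,000 to 400,000 trials, pooled variance, equal SDs):

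| Quantity | Gate + Bonferroni (planned) | Gate, pairs at 5% |
|---|---|---|
| Design point: each relapse contrast | 62% | 73% |
| Design point: both relapse contrasts | 47% | 65% |
| Design point: at least one relapse contrast | 77% | 80% |
| Evenly spaced: extreme pair | 62% | 66% |
| Evenly spaced: adjacent pair | 15% | 26% |
| Family-wise error, all means equal | 4.2% | 5.0% |
| Family-wise error, one group far apart | 1.7% | 5.0% |

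Before rounding, the evenly spaced losses are about 4.6 points (extreme pair) and 11 points (adjacent pair).

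**5. Unequal variances.** The article gives no SDs, so the ratios are assumptions. Let both patient groups have equal means and a larger SD than the controls, with the control mean far away. The error for relapse against remission is then:

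| Patient SD / control SD | Pooled, planned | Pooled, pairs at 5% | Welch gate, Welch pairs at 5% |
|---|---|---|---|
| 1.5 | 3.0% | 7.6% | 4.9% |
| 2 | 3.8% | 9.0% | 5.0% |

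At equal variances the Welch version keeps the gain: 61% rises to 72% per relapse contrast at the design point.

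**The case against.** The strongest reply is that nothing here is wrong. ANOVA followed by Bonferroni is standard, valid and conservative, and choosing otherwise is a preference between two valid methods. That stands as far as validity goes: this is an inefficiency, and a reader should not infer that the plan's error control fails. It is still more than taste, because the stated 5% target can be met with more power at no cost in patients.

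Three further points stand and limit the claim.

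- **Error does fall.** A reader might infer that Bonferroni buys nothing. It does lower the actual error, to between 1.7% and 4.2%. It is unnecessary only relative to the 5% target, and the article sets no stricter one.
- **Variance.** Simply deleting the Bonferroni step while keeping pooled-variance pairs would be unsafe. If patients vary more than controls, that step incidentally protects the relapse-against-remission contrast. The failure lies in the pooled test and not in the closure argument, and separate-variance tests remove it.
- **Across markers.** The article lists ten primary markers, and Bonferroni is the only multiplicity control that it states. Testing pairs at 5% raises the per-pair error from 1.7% to 5% in a marker where one group stands apart. The argument here gives no licence on multiplicity across markers.

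It is also fair to say that success on both relapse contrasts is nowhere a stated criterion, so the 18-point figure describes one possible aim and not a planned endpoint.

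**Conclusion.** The Bonferroni step is redundant for holding the within-marker family-wise error at 5%, because there are exactly three groups and a significant omnibus test is already required. At the layout behind the stated 80%, it costs about 11 points of power per relapse contrast and 18 for declaring both.

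A reader might take 11 to 18 points as a general loss, but it belongs to that layout. With evenly spaced means the extreme pair loses about 5 points and an adjacent pair 11, and the chance of at least one relapse contrast at the design point falls by only about 3.

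The same loss should not be read into the rank route as though it were planned, because the article states no post-hoc rule after Kruskal-Wallis. If Bonferroni is assumed there too, simulation gives a similar per-contrast comparison (58% against 69%).

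The conclusion rests on two-sided tests, a correction over three pairs, and pairwise tests that are valid under unequal variances. The change is worth making, but the trial's validity does not depend on it.

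**What to change.** In Statistical Methods, replace the Bonferroni sentence with: *If the three-group test (Welch ANOVA) is significant at level alpha, each of the three pairs is tested at the same alpha with its own two-sample separate-variance (Welch) test, not with the pooled ANOVA variance (closed testing, valid for exactly three groups).* Add that any stricter alpha set across the ten primary markers applies to both the gate and the pairs. Make the change before group results are seen.

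The cost is a sentence or two of text, with no extra patients or assays. There are three downsides:

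- The actual within-marker error rises from 1.7%–4.2% to the nominal 5%.
- The unadjusted pairwise confidence intervals are not simultaneous. Bonferroni intervals can be kept as descriptive output.
- Analysts must not fall back on pooled-variance post-hoc pairs.

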## Discussion

While we await our results, we discuss here the methods chosen to conduct our study.

### Blood Count Test

Gens et al. examined 2.145 whole blood samples to evaluate the analytical performance between two hematology analyzers: Sysmex XN 3000 and UniCel DxH 800. For both analyzers, the variation coefficients (CV%) for hemoglobin, RBC, MCV, WBC were <5%, for WBC less than 10%, while the variation coefficients for platelets and monocytes were <5%, 15%, 6%, and 9.5%, 45%, respectively for Sysmex XN 3000 and DxH 800. The analyzers are equally precise (R>.86), with the exception of monocytes and basophils (99).

Barnes and his collaborators furthermore evaluated a better sensitivity and specificity of the DxH 800 analyzer compared to the previous Beckman Coulter LH 750 series. The DxH 800 instrument is more skilled in capturing explosions; in fact, out of 95 samples containing a burst percentage > or = 1%, the LH 750 detected 6.4% of false negatives, while the DxH 800 0.0%. The advantage of having a low false positive number has reduced peripheral blood smears for microscopic blood analysis, a time-consuming technique, and the use of an expert operator (100).

In another study, the Beckman Coulter UniCel^®^ DxH 800 analyzer was compared with the Coulter^®^ LH 780 and flow cytometry (FCM), and it was found that the DxH 800 instrument has greater sensitivity and specificity for counting WBC, PLT, and NRBC with fewer false negatives for NRBC compared to LH 780 and greater accuracy for PLT and NRBC counting than FCM (101).

### Angiopoietin-1, Angiopoietin-2, FIII/TF, TM, Tie-2, VEGF

The ELISA is the most commonly used method in both diagnostics and clinical research. However, it has some limitations. This technique requires large volumes of sample to capture an antigen of interest. In some cases, the larger surface of the wells can favor non-specific bonds, and the resulting fluorescence signal is not always linear and may invalidate the test. The assay performed on multiplex platforms also allows greater flexibility, reduced sample volume, and lower cost, with a similar workflow. Luminex xMAP technology is an array platform that allows both monoplex and multiplex assays that can be applied to either protein or nucleic acid applications. Microspheres have a smaller surface and the non-specific bond is significantly reduced (102).

Using multi-array and electrochemiluminescence technologies, the MSD platform offers multiplex capability with a consistency similar to that observed in ELISA with reduced costs and labor (103).

### Coagulation Parameters

Laboratory automation began many years ago and has since spread across other fields such as hematology, immunology, molecular biology, and coagulation tests. The advantages of automation are either standardization, error reduction, cost reduction, or productivity increase, whereas the only disadvantage is its high maintenance costs (104).

The hemostatic measurements are influenced by the technique of the instrument and the reagents used for individual analyzes (105).

Geens and his collaborators compared the performance of System CS5100 and Stago STA-R analyzers for determining routine coagulation parameters such as aPTT, PT, FBG, DD, and AT (106).

All parameters including imprecision, accuracy, and total error were deemed acceptable for the two methods; however, the difference between them consists of both high sensitivity of the CS5100 for APTT towards the deficiencies of the factors and presence of unfractionated heparin.

Unlike Stago STA-R analyzers, the CS5100 can automatically control pre-analytical variable such as sample volume and interfering substances such as hemolysis, hyperbilirubin-hememia, and lipemia but fails to analyze highly lipemic and icteric samples that represent a disadvantage in routine practice.

The APTT reagent of CS5100 showed sensitivity between 46% and 72% to FVIII, IX, XI, and XII factors while the PT reagent showed sensitivity between 34% and 52% to FII, FV, FXII, and FX factors. This explains the reference interval for APTT between the two instruments (23–31s on CS5100 vs. 30–42s on STA-R Evolution).

Furthermore, a small increase in the percentage of PT and a slight decrease in PT (INR) and FBG on the CS5100 was observed compared to the STA-R Evolution instrument (106).

Hemolysis (4%), hyperbilirubinemia (11%), and lipemia (13%) are the main preanalytical variables that cause errors in blood sample coagulation tests (107).

Woo-Jae Kwoun and coworkers assessed the performance of the pre-analytic module of the ACL TOP 750 analyzer where the reference values obtained were compared with those of the XPT instrument for chemistry, which uses an enzymatic method, and with those of ADVIA2120i, which uses a spectrophotometric method (108). The researchers concluded that an efficient control of the pre-analytical variables is exercised by the ACL TOP family series 50 spectrophotometric apparatus module ensuring sample quality monitoring, while accurate test results from the interference of the HIL sample.

The ACL-TOP analysis system produces three types of curves. The first curve shows changes in absorbance during aPTT measurement. The second one, derived from absorbance, is related to the speed of coagulation. The third one measures the acceleration of coagulation. Tokunaga and his collaborators noted the second derivative curve’s utility for detecting factor deficiencies (109). Shortcomings were found not only in FVIII but also in FIX, FXI, FXII, and FV. It has been reported that the ACL TOP system that uses the APTT-SP reagent comprising silica to be the most suitable for detecting intrinsic deficiencies of coagulation (110). Monitoring vWF on plasma from patients with acquired von Willebrand syndrome was evaluated and showed less than 10% of the activity of the vWF cofactor of both ristocetin and vWF antigen (111). After 15 minutes of desmopressin infusion (vasopressin 1-deamin-8-D-arginine; DDAVP), and based on the variations of the waveforms in an aPTT assay on the second derivative curve, levels of vWF and FVIII remarkably increased to 54% and 84%, respectively (111). These results explain that the waveform analysis of the second derivative curves of an APTT assay provide useful information relating to both reduction of coagulation factors and therapeutic treatment.

The ACL TOP instrument efficiently performs specific and routine coagulation tests for up to 120 samples simultaneously with high quality starting from smaller samples and reagent volumes rather than manual methods. Its use in many laboratories is determined by either its precision, reliability, high productivity, or daily maintenance of 4 minutes.

It is also equipped with a software capable of rerunning automatically multiple tests simultaneously using different dilutions.

The intra-assay and inter-assay precision (coefficients of variation) were less than 5% for most coagulation parameters in both the normal and pathological range (112). The results of coagulation tests obtained by the ACL TOP are well correlated with those obtained on the STAR analyzer characterized by a correlation coefficient (r) ranging from 0.876 to 0.990 (113).

#### Complement

It is necessary to standardize tests evaluating the function of the classical, alternative, or lectin pathway since the analysis of the complement system, with the exception of some proteins such as C3 and C4, varies widely between laboratories. Autoantibodies such as anti-C1q, convertases C3 and C4, or regulatory proteins like inhibitor of anti-C1, anti-factor H, are relevant in defining autoimmune processes and diseases based on complement dysregulation. The standardization committee of the International Complement Society (ICS) and the International Union of Immunological Societies (IUIS) have provided guidelines that ensure the quality of tests for the complement analysis (114).

Laboratory analyses for triggering the activation of the classical complement pathway are performed with methods based on the principles of nephelometry, turbidimetry, and ELISA (115). Complement deficiency is commonly detected in the laboratory by quantifying the main soluble fragments C3 and C4 formed during activation.

Li H. and his colleagues measured complement levels C3 and C4 in Chinese patients with systemic lupus erythematosus (SLE). The complement assay was performed based on the dispersion turbidimetry immunization rate using the Beckman Coulter instrument (Inc. Brea, CA, USA). The reference values for C3 were between 0.79 and 1.52 g/L and those for C4 were between 0.16 and 0.38 g/L, in line with those used in our laboratory measured by immunoturbidimetry and the COBAS 8000 instrument (116).

A recent study compared the levels of C3 and C4 fragments of patients diagnosed with SLE with those of healthy subjects by nephelometry. C3 and C4 values were significantly higher (p <0.001) in healthy subjects than in patients.

Sensitivity and specificity for complement C3 are 87.11% and 82.74%, respectively, and for complement C4 are 88.66% and 77.43%, respectively (117).

Myriam and his collaborators studied the activation product of plasma complement C4d of patients with SLE as a marker of lupus nephritis by ELISA. The test found significantly higher C4d values in SLE patients compared with healthy subjects, whose C4d levels were negligible.

Levels of C4d discriminated the highest and lowest clinical disease activity with a positive predictive value of 68% and a sensitivity of 79% for identifying patients with nephritis. The test could detect the lowest concentration of 5.6 μg/L. The precision of the test was demonstrated by the intra-assay and inter-assay coefficients of variation of 13.2% and 16.7%, respectively (118).

According to a previous study regarding good monitoring of C4d marker disease, the availability and ease of the test, long execution times, probable sources of error by the operator, and detectable false positives are all disadvantages.

#### Antiphospholipid Antibodies

The laboratory criteria for APS were revised and published in 2006 due to the heterogeneity of aPL, plasma proteins, or protein complexes related to them, as well as to the harmonization of the assays diagnosing the APS in order to improve the detection of aPL antibodies and the interpretation of the results (119).

The new criteria include the LAC test, aCL IgG/IgM, and aβ2GPI IgG/IgM, measured by different types of solid phase immunoassays. Currently, these immunoassays have not been entirely standardized (120).

The aPL immunological test provides information that was not obtained from the LAC test such as specific antiphospholipid analytes, isotypic class (IgM or IgG), and their concentration levels. The solid phase of the immunoassay is important and should not be influenced by analytical variables, like anticoagulant or anticoagulant therapy, as they represent interference factors for the LAC test.

In addition to the ELISA test, either chemiluminescence immunoassays (CIA), enzyme fluorescence immunoassays, or new emerging technologies such as multiple dosing through microspheres are widely used in clinical diagnostic laboratories (119). CIAs have recently been developed for the detection of aPL antibodies and are currently used in a number of clinical laboratories. CIAs are advantageous due to their extreme sensitivity and capability to be automated (121).

A number of studies have demonstrated that the performance of CIAs is similar to both commercial and laboratory developed ELISAs for aPL criteria (122).

It has recently been suggested that CIAs improve reproducibility and inter-laboratory correlations for these analytes (123).

Despite these developments, there are still no generally accepted reference reagents for the development and calibration of these tests. It is necessary to compare the performance of the new methods used for detecting aPL antibodies with the more traditional ELISA adopted to identify the commutability in the diagnosis of the APS.

Testing for aPL antibodies has traditionally been performed by ELISA due to both easy use and widespread availability (124).

Thomas B. Martins and his collaborators evaluated methods for detecting aCL and aβ2GPI antibodies in patients with APS, and concluded that the two methods are comparable; however, CIA was found to be more sensitive in detecting aβ2GPI IgG while ELISA was more sensitive to aCL IgM. Lastly, the CIA compared to ELISA method was associated with a higher number of LAC-positive APS patients.

In agreement with this, a more recent study showed a good correlation (> 80%) between the ELISA and CIA methods (125). This is also evident in the study of the Iwaniev et al., which, however, reported a significantly lower detection of IgM aCL antibodies (126).

